#### Nursing records

3.2.2

By using a web‐based random generator, a sample of nursing records (*N = *180) will be drawn (https://www.random.org/). Nursing records covering at least 4 days and at least one nursing diagnosis will be selected from all six wards (experimental group *N = *90, control group *N = *90). The sample‐size calculation was performed using *t*‐tests for unpaired samples (one‐sided) and bases on previous results for using the Q‐DIO for all three sub‐concepts of the instrument (nursing diagnoses, interventions and outcomes) (Müller‐Staub, Needham, et al., 2008). An effect size of 0.5 (mean) on a scale from 0–4 is assumed. For nursing diagnoses, 32 nursing records per group are required; we assumed an effect size of 0.63 (power 80%). For nursing interventions, 45 records (effect size, 0.53; power, 80%) are required and for nursing outcomes, 44 records (effect size, 0.47; power, 70%) are required. To ensure an even distribution in the experimental and control groups, 15 nursing records will be selected per ward (*N = *45 records before and 45 records after the study intervention, totalling *N = *90) for each group (Bortz & Schuster, 2016).

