### Expected outcomes

3.4

The primary outcomes are the level of the nurses’ knowledge, the level of their attitude, satisfaction with GCR, the quality of nursing diagnoses, interventions and outcomes and the frequency and variety of NANDA‐I‐nursing diagnoses (Doenges et al., 2014; NANDA‐I, 2016). The secondary outcomes are nurses’ behaviour in the field of work (clinical performance of the Advanced Nursing Process evaluated by observations and by patient interviews) and mutual comparisons of all findings.

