### Data analyses

3.6

The knowledge test and nurses’ attitude (PND scale) will be analysed using descriptive and inductive statistics. Single‐item and total scores will be compared between the two measurement points (Wilcoxon signed‐rank test) and between the experimental and control groups (Mann–Whitney *U* tests). The scores of supplementary control items for the knowledge test will be separately analysed and compared between the two measurement points and the two groups. The results of the three nurses’ attitude measurements (*t*0_2_, *t*1 and *t*2) will be evaluated using Friedman tests (Bortz & Schuster, 2016; Clauß, Finze, & Partzsch, 2011). The free‐text item answers in the knowledge test will be analysed using Mayring's (2010) seven‐step content analyses.

Participant satisfaction will be descriptively analysed based on absolute and relative frequencies and distributions. Content analyses (Mayring, 2010) will be applied to the interview with the nursing director and to the free‐text data from the satisfaction surveys.

The Q‐DIO R scores will be summed for each sub‐concept. If the data are normally distributed, unpaired *t*‐tests are applied to compare pre‐ and postintervention scores and to compare the experimental and control groups. The frequencies and patterns (variety) of the NANDA‐I nursing diagnoses will be compared between the two measurement time points and between the experimental and control groups.

Correlations among nurses’ knowledge, attitude, Q‐DIO R scores, demographic and organizational characteristics will be analysed depending on level of data and testing requirements by Pearson product–moment correlations, Spearman correlations or chi‐squared tests. All tests will be evaluated one‐sided (levels of significance 0.05) using IBM SPSS Statistics 24 (SPSS Inc.).

The qualitative evaluation of nurses’ clinical behaviour will be performed by within‐ and cross‐case analyses (Kuckartz, 2016). Qualitative observations, interviews and nursing records will be analysed using the first and second coding cycles (Saldaña, 2015). Decoding (open) is applied in the first cycle, and encoding (deductive) is applied in the second cycle. For the qualitative data analyses, MAXQDA 12 software (VERBI GmbH, 2015) will be used.

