## CONCLUSION

5

This study protocol has outlined the rationale and design to examine the effectiveness of GCR. If the training participants and the nursing director are satisfied with GCR and if it leads to enhanced nurse knowledge, attitudes and clinical performance as well as to a higher quality of nursing diagnoses, interventions and outcomes, then replications in other settings and places can be suggested. If the study hypotheses are supported, recommendations can be provided on using GCR in practice to enhance the application of the Advanced Nursing Process.

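### One-sided 0.05 is set for every test, including tests and analyses without a direction, and eight primary outcomes are listed with no confirmatory order

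*Protocol article*

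**What the plan says.** Section 3.4 (Expected outcomes) opens its list with "The primary outcomes are the level of" knowledge among the nurses. It goes on to attitude, satisfaction and the quality of three parts of the record (diagnoses, interventions, outcomes), and it ends with "the frequency and variety of NANDA‐I‐nursing diagnoses". Counted separately these are eight: knowledge, attitude, satisfaction, three Q-DIO R sub-concepts, frequency and variety. None is ranked above another.

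Section 3.6 (Data analyses) treats them differently:

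- **Knowledge and attitude:** single items and totals are compared over time (Wilcoxon) and between groups (Mann–Whitney).
- **Attitude at three time points:** the measurements "will be evaluated using Friedman tests".
- **Q-DIO R:** each sub-concept sum gets unpaired t-tests if the data are normal.
- **Frequency and variety:** compared, with no test named.
- **Satisfaction:** "Participant satisfaction will be descriptively analysed based on absolute and relative frequencies and distributions".
- **Associations with demographic and organizational data:** Pearson or Spearman correlations or chi-squared tests.

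The section then sets one rule for everything: "All tests will be evaluated one‐sided (levels of significance 0.05).

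Section 3.2.2 (Nursing records) bases the sample size on t-"tests for unpaired samples (one‐sided) and bases on previous results for using the Q‐DIO for all three sub‐concepts". The Conclusion says: "If the study hypotheses are supported, recommendations can be provided on using GCR in practice".

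**The concern.** There are two linked problems.

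First, a one-sided rule needs a direction stated in advance. Section 2.4 (Hypotheses) gives one for the knowledge total, the PND attitude score and Q-DIO R quality. The rule in section 3.6 reaches further. It covers a Friedman test, which asks only whether three measurements differ. It covers chi-squared tests, which have a direction only in a 2x2 table, through the signed root. It also covers the control items on content that the training does not teach, and correlations with demographic and organizational factors. Section 2.4 gives no direction for either.

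Second, the article does not say which primary outcomes are confirmatory, in what order, or whether one success is enough or all are needed. The two readings carry opposite risks: inflated false-positive error under the first, and power below the stated figures under the second. Practice recommendations are to follow from the hypotheses, so the reading has to be settled before the data are analysed.

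**Working it through.** **1. Reproducing the sample size.** Inputs from section 3.2.2 are standardised effects 0.63, 0.53 and 0.47 with power 80%, 80% and 70%. Alpha 0.05 one-sided comes from section 3.6. The exact two-sample t calculation gives:

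| Sub-concept | Stated n per group | One-sided 0.05 | Two-sided 0.05 |
|---|---|---|---|
| Diagnoses | 32 | 31.9 → 32 | 40.5 → 41 |
| Interventions | 45 | 44.7 → 45 | 56.9 → 57 |
| Outcomes | 44 | 43.3 → 44 | 56.9 → 57 |

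The stated figures reproduce only with a full, unadjusted one-sided 0.05 for each sub-concept. The calculation is correct on its own terms, and no alpha is shared between the three.

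**2. Direction of the Friedman test.** The statistic is built from squared deviations of rank sums. On one simulated data set of 34 nurses and three time points it was 10.12 (p = 0.0064), and reversing the sign of every score gave the same value. Improvement and deterioration are therefore indistinguishable to it. With 2 degrees of freedom the 5% cut-off is 5.99. Rejecting when half the p-value is below 0.05 means rejecting when p is below 0.10, a cut-off of 4.61. Simulated error under no effect was 5.4% at 5.99 and 10.2% at 4.61. The halving arithmetic is the same for a general chi-squared table.

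**3. Any one outcome suffices.** The chance of at least one false positive in k independent tests is 1 − 0.95^k.

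- Five outcomes with a named test (knowledge, attitude, three sub-concepts), one comparison each: 1 − 0.95^5 = 0.226.
- Seven, if frequency and variety are also tested: 1 − 0.95^7 = 0.302.
- With an assumed common correlation of 0.5 between test statistics: about 0.17 and 0.20.

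The article gives no correlation between outcomes. The independence values are upper figures if the correlations are positive.

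**4. All three sub-concepts needed.** There are 45 post-intervention records per group (15 per ward × 3 wards). One-sided 0.05 power is 0.907, 0.802 and 0.715 at the three effect sizes.

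- Independent: 0.907 × 0.802 × 0.715 = 0.520.
- Assumed common correlation 0.7: about 0.64.

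Both treat records as independent, so clustering by ward is not yet counted.

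**5. Is an order stated elsewhere?** Section 3.6 ends with a chain of evidence in which a positive lower Kirkpatrick level is needed before the next. No alpha rule is attached. Level 1 is descriptive and level 3 qualitative, while levels 2 and 4 each hold several outcomes. Within level 2 alone, two independent tests give 1 − 0.95^2 = 0.0975.

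**The case against.** The case for leaving the plan alone has real substance.

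- **The main hypotheses are directional and the sample size is one-sided throughout.** This stands. One-sided testing of those comparisons is consistent, and a demand for two-sided tests everywhere would be a preference.
- **Nothing says that p-values will be halved.** This also stands. Friedman and chi-squared tests reject in the upper tail, and their ordinary p-value at 0.05 keeps the 5% level. The 10% is conditional on how the rule is carried out, but the rule as written leaves that open.
- **The Conclusion does not rest on one lucky result.** A reader might infer that a positive finding anywhere leads to recommendations. The article does not support that. The condition for suggesting replication joins satisfaction, knowledge, attitudes, clinical performance and quality, and the recommendation sentence speaks of hypotheses in the plural. The 23% and 30% therefore describe one possible reading, not a stated decision rule.
- **Eight outcomes are not eight tests.** A reader might count all eight, but satisfaction is never tested. A reader might also compound the single items as if independent. The Cronbach's alpha of 0.96 cited for the 20-item PND contradicts that: it implies a mean inter-item correlation of 0.96 / (20 − 19 × 0.96) = 0.55. Single items also appear in no hypothesis.
- **Some correlations have an expected direction.** The Background treats knowledge and attitude as influences on how the process is applied. The point is limited to demographic and organizational correlates and the control items.
- **A multiplicity adjustment may sit in an analysis plan not shown.** It may, and its absence is not the finding. The unranked primary list and the universal one-sided rule are written in this document.

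**Conclusion.** The concern holds in limited form. The universal one-sided rule is wrong as written for the three-period Friedman test, for chi-squared tests beyond 2x2, and for the control-item and demographic or organizational correlation analyses. The error would reach about 10% if Friedman or chi-squared p-values were halved.

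The primary list needs a stated confirmatory role for each outcome. If any one outcome may carry a claim, the false-positive chance is up to 23% (five tests) or 30% (seven) under independence, and less with positive correlation. If hypothesis 3 requires all three sub-concepts, joint power is about 52% (independent) to 64% (correlation 0.7), against the 70% to 80% stated for each one separately. That range takes the article's effect sizes as given and ignores clustering. The article does not claim joint power, and the two risks do not apply to the same claim at once.

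**What to change.** 1. In section 3.6, limit one-sided 0.05 to the directional comparisons in section 2.4.
2. Report Friedman, general chi-squared, control-item and demographic or organizational correlation analyses with ordinary non-directional p-values at 0.05.
3. In section 3.4, state the confirmatory order before analysis. One example is the Q-DIO R sub-concepts in fixed sequence (diagnoses, interventions, outcomes), because the sample size rests on them. Each step is tested at full one-sided 0.05 only if the one before succeeds.
4. Say whether hypothesis 3 needs one sub-concept or all three.
5. Label satisfaction as descriptive, and single items and correlations as exploratory without significance claims.

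The cost is fewer formal claims and a dated amendment, since section 3.7 says data collection has started. No new data are needed.

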### Ethical considerations

3.7

This study was authorized by the regional ethics committee in April 2016 (Nr. PB_2016_00990), and data collection has started. The study will be executed in conformity with the Declaration of Helsinki (WMA, 2013) and with Good clinical practices (Altpeter et al., 2005).

The nurses and the nursing director will be asked for voluntary participation. Nursing records from the archives (pre‐intervention data) were permitted to be retrieved without patients’ informed consent. Written informed consent will be obtained for postintervention document analyses, for patient observations and for interviews. Comprehensive written and oral information on the study aim and procedures, together with descriptions of the patients’ rights as study participants, will be provided at least 1 day before data collection.

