#### Measurement time points before and after the GCR study intervention

3.5.2

Data collection will occur at three time points; the flow chart in Figure 3 presents all data collection methods and time points. As baseline measurement before the GCR intervention (*t*0_1_ + *t*0_2, _illustrated in boxes): a sample of nursing records will be drawn, and nurses of the intervention and control group perform the knowledge tests and all nurses of the participating wards fill out the PND scales (illustrated in circles). After GCR, the participants complete knowledge tests and PNDs for the second time and complete the satisfaction survey (*t*1). After ending of the GCR intervention, all nurses complete the PND a second and a third time. At that time, a second sample of nursing records will be drawn. In addition, patient care will be observed (nurses’ clinical performance) and patients are interviewed to cross‐validate the Q‐DIO R results on the quality of the Advanced Nursing Process as described in the nursing records.

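### Baseline records need no patient consent but post-intervention records do, so the within-arm pre-post t-test of Q-DIO R scores compares differently selected samples

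*Protocol article*

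**What the plan says.** Under Ethical considerations, archived pre-intervention records "were permitted to be retrieved without patients’ informed consent". For the later period the rule changes: "Written informed consent will be obtained for postintervention document analyses".

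The section on measurement time points makes clear that the later records are a separate draw: "a second sample of nursing records will be drawn". The Nursing records section gives one set of eligibility criteria, with no mention of consent: "Nursing records covering at least 4 days and at least one nursing diagnosis will be selected from all six wards". Each group contributes "45 records before and 45 records after the study intervention".

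In the Data analyses section, if the data are normal, unpaired "tests are applied to compare pre‐ and postintervention scores and to compare the experimental and control groups". All tests there are one-sided at 0.05. The frequency and variety of nursing diagnoses are also to be compared between the two time points and between groups, with no test named. No contrast of the change in one arm with the change in the other is described.

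Hypothesis 3 concerns the experimental group against the control group after GCR. The Limitations section does not mention the difference in consent rules.

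**The concern.** An unpaired pre-post test can be read as a change in documentation quality only if the two sets of records come from comparable patients. Here the baseline set is a random draw from archived records that meet the length and diagnosis criteria. The later set must meet those criteria and also have consent. If the records of patients who consent differ in quality from those of patients who do not, the mean score moves between periods even when nurses document exactly as before.

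The quality of diagnoses, interventions and outcomes is listed among the primary outcomes, and a one-sided test at 0.05 is attached to this comparison. A significant pre-post rise in the experimental arm could then be reported as a GCR effect when part or all of it is selection. A true rise could equally be hidden.

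**Working it through.** **Inputs from the protocol article**
- Records per arm and period: 45 before, 45 after (Nursing records).
- Test: unpaired t-test, one-sided, alpha 0.05 (Data analyses).
- Planned effect sizes and power: diagnoses 0.63 at 80%, interventions 0.53 at 80%, outcomes 0.47 at 70% (Nursing records).

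**The plan's own figures first.** The exact one-sided two-sample t-test gives 31.9, 44.7 and 43.3 records per group. Rounded up, these are 32, 45 and 44, as stated. The sample-size arithmetic is sound; the issue is the design of one comparison.

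**Inputs that the documents do not give (assumptions)**
- Consent rate c: 50%, 70% or 90%.
- Difference g between the mean scores of consenters and non-consenters: 0.2, 0.3 or 0.5 SD.

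**Formula.** If the baseline sample contains both kinds of patient in the proportions c and 1 − c, its mean is c × (consenter mean) + (1 − c) × (non-consenter mean). The later sample has the consenter mean. The spurious shift is therefore

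shift = (1 − c) × g.

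The rejection rate below is that of the one-sided t-test at 45 against 45 when the only difference is this shift and consenters score higher. The last column is the shift divided by 0.53, the effect size planned for interventions.

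| Consent rate | g (SD) | Shift (SD) | Rejection rate with no true change | Share of 0.53 |
|---|---|---|---|---|
| 90% | 0.2 | 0.02 | 6.0% | 4% |
| 90% | 0.3 | 0.03 | 6.6% | 6% |
| 90% | 0.5 | 0.05 | 7.9% | 9% |
| 70% | 0.2 | 0.06 | 8.7% | 11% |
| 70% | 0.3 | 0.09 | 11.1% | 17% |
| 70% | 0.5 | 0.15 | 17.4% | 28% |
| 50% | 0.2 | 0.10 | 12.0% | 19% |
| 50% | 0.3 | 0.15 | 17.4% | 28% |
| 50% | 0.5 | 0.25 | 32.0% | 47% |

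**Opposite direction.** If consenters score lower, the shift is subtracted from a true effect. For interventions, power at 45 against 45 is 80% with the full 0.53. With 0.53 − 0.02 = 0.51 it is about 78%, and with 0.53 − 0.25 = 0.28 about 37%.

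**Comparison between arms.** Let s be a shift common to both arms, and let E and C be the true post-intervention means without it. The post-intervention contrast is (E + s) − (C + s) = E − C. The contrast of changes is (E + s − E0) − (C + s − C0) = (E − E0) − (C − C0), where E0 and C0 are the baseline means. In both, s cancels. If the shifts differ by arm, the difference between them remains.

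**Precision.** Ignoring ward effects, the standard error of the post-intervention contrast is √(1/45 + 1/45) = 0.21 SD. That of the contrast of changes is √(4/45) = 0.30 SD. With only six wards, the ward-level uncertainty comes on top.

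**The case against.** The strongest reply is that the stated hypothesis is not the pre-post comparison. Hypothesis 3 sets the experimental arm against the control arm after GCR, both arms pass the same consent filter at that point, and the comparison is already in the Data analyses section. That stands, and it limits the point to the within-arm test. It does not remove the point: the plan attaches a one-sided test to the pre-post comparison of a primary outcome, gives no rule for reading it, and plans no contrast that would set the control arm's change against it.

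It is also true that the size and direction of any bias are unknown. At 90% consent and a 0.2 SD difference, the error rate hardly moves. The consent asymmetry follows from what was permitted for archived records and was not a free statistical choice.

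A reader might go further and infer several things that the documents do not support:
- That the archive sample contains confused, very ill or unwilling patients. Nothing describes its make-up; one can say only that no such exclusion is stated for records. The orientation and language criteria are set for the 24 interviewed and observed patients.
- That only patients able to sign for themselves can enter the later sample. The article does not say who signs.
- That nurses know in advance whose record will be audited. Information is due at least one day before data collection, which for a record audit could fall after the charting is done.
- That frequency and variety are subjected to a pre-post significance test. They are to be compared, but no test is named.
- That the comparison between arms is biased. It would be only if consent differed by arm, and the documents contain no evidence on that.

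**Conclusion.** The point holds for the within-arm pre-post comparison. The article fixes both the unequal consent rule and a one-sided test that takes no account of it, so a pre-post p-value cannot be read as an effect of GCR alone. This is not a detail left to a fuller document, because both elements are stated.

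The documents do not allow the size to be estimated. Under the assumed consent rates of 50-90% and differences of 0.2-0.5 SD, the spurious shift is 0.02-0.25 SD. The nominal 5% error becomes about 6-32% if consenters score higher, and power falls if they score lower. The ranges are illustrations and rest wholly on those assumptions.

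The post-intervention contrast of Hypothesis 3 stands as planned with respect to this issue, provided that consent does not differ between arms. The sample-size figures are not in question.

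**What to change.** In the Data analyses section:

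1. State that the within-arm pre-post comparisons of Q-DIO R scores, and of the frequency and variety of diagnoses, are descriptive.
2. Base the conclusion about GCR on the concurrent comparison of experimental and control arms. Use the baseline records already planned through a group-by-period contrast or adjustment for ward baseline, with an analysis that allows for only six wards. Either form cancels a consent effect common to both arms.
3. Report the numbers of patients approached and consenting, per ward and arm, so that readers can judge whether consent was similar. Data collection has started, so the counts should be logged from now on; they may not be recoverable later.
4. If baseline records are restricted to patients who could have consented, do so only as a sensitivity analysis. The restriction reduces the 45 baseline records per arm and cannot identify patients who would have been unwilling. For example, an assumed 30% exclusion leaves 0.70 × 45 = 31.5, about 31 or 32, against the 45 that the plan requires for interventions.

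The change needs new analysis wording and a simple consent log, and leaves the consent arrangements as they are. The cost is that pre-post p-values no longer serve as evidence of effect, and that a contrast resting on six wards is less precise. A one-sentence acknowledgement of the consent asymmetry belongs in the Limitations section.
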